## 8. Outcomes

Both groups will undergo standardized assessments at baseline (T0), mid-treatment (4 weeks, T1), post-treatment (8 weeks, T2), and at follow-up timepoints (16 weeks, T3; 24 weeks, T4). Evaluations will include cardiopulmonary functional performance, echocardiographic measurements, biochemical markers, cognitive function, and QoL (Table 3).

The primary outcome of the study is the improvement in functional capacity, assessed as a ≥10% increase in VO_2_max, measured via CPET at 8 weeks (T2).

Secondary outcomes include:QoL: Assessed using the KCCQ-12 and SF-36 at each timepoint.Biochemical parameters: Changes in BNP, NT-proBNP, creatinine, eGFR, serum electrolytes (sodium, potassium, chloride), glucose, and lipid profile.Functional assessments: Performance on the 6MWT and SPPB.Cognitive status: Assessed with the MMSE.Echocardiographic parameters: Left ventricular ejection fraction (LVEF), diastolic function indices (E/A—Ratio of early E to late A ventricular filling velocities; E/e’—Ratio of early transmitral flow velocity to early diastolic mitral annular velocity), and right ventricular function (TAPSE—Tricuspid Annular Plane Systolic Excursion, RVs’—Right Ventricular Systolic Velocity).Adverse events: Monitoring of any complications related to training or telemonitoring (e.g., hypotension, arrhythmias, device issues).

These outcome measures will allow for a comprehensive and longitudinal evaluation of the effects of both in-person and telehealth cardiac rehabilitation on patients with chronic heart failure.

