## 9. Statistical Analysis

### 9.1. Primary Endpoint Analysis

To evaluate the primary endpoint of the study—defined as a ≥10% improvement in VO_2_max at 8 weeks—paired comparisons between baseline and post-intervention values will be performed using a paired t-test for normally distributed data [36,37,38]. For non-normally distributed data, the Wilcoxon Signed-Rank test will be applied. Additionally, the proportion of patients achieving the predefined VO_2_max improvement threshold will be analyzed using logistic regression, with “Rehabilitation Type (Telerehabilitation vs. Standard)” as the main predictor. The model will be adjusted for clinically relevant covariates identified through baseline comparisons using ANOVA or chi-square tests. Odds ratios and 90% confidence intervals will be reported.

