### 9.2. Secondary Endpoint Analysis

Continuous variables will be presented as mean ± standard deviation for normally distributed variables, and as median and interquartile range for those with non-normal distribution. Categorical data will be expressed as absolute numbers and percentages. The Shapiro–Wilk test will be used to assess normality.

For repeated measurements (e.g., QoL scores, biochemical markers, functional parameters), comparisons across timepoints (T0, T1, T2, T3, T4) will be conducted using one-way repeated measures ANOVA for normally distributed data, or Friedman test for non-parametric data.For post hoc comparisons, Bonferroni correction will be applied to control for type I error.Categorical variables (e.g., proportion of patients with adverse events) will be compared using the Pearson chi-square test or Fisher’s exact test where appropriate.

A two-sided *p*-value < 0.05 will be considered statistically significant for all final analyses.

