### 9.3. Sample Size Calculation

Based on the primary endpoint, the required sample size was calculated using G*Power software (Version 3.1.9.7). Assuming a 10% increase in VO_2_max in the intervention group compared to the control group, with a two-sided alpha level of 0.05 and statistical power (1–β) of 90%, the estimated sample size is 200 patients.

To compensate for a potential 10% dropout rate, the final target enrollment is 220 patients with CHF. This sample size is considered sufficient to detect clinically relevant differences in functional capacity and allows for robust evaluation of secondary outcomes including QoL, echocardiographic and biochemical parameters.

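### The primary odds ratio is to be reported with a 90% confidence interval, which does not match the two-sided 0.05 level set for the plan's tests and sample size

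*Protocol article*

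**What the plan says.** All places are in the protocol article.

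- **Section 8 (Outcomes)** makes the primary outcome binary: a patient responds if VO2max has risen by at least 10% at 8 weeks.
- **Section 9.1 (Primary Endpoint Analysis)** compares responder proportions by logistic regression, with telerehabilitation versus standard rehabilitation as the main predictor and adjustment for covariates. It then states: "Odds ratios and 90% confidence intervals will be reported". The paired t-test and Wilcoxon signed-rank test in the same section compare baseline with post-intervention values, so the odds ratio is the only between-arm estimate named for the primary endpoint.
- **Section 9.2 (Secondary Endpoint Analysis)** closes with the significance rule: a two-sided p-"value < 0.05 will be considered statistically significant for all final analyses".
- **Section 9.3 (Sample Size Calculation)** bases the sample size on the primary endpoint, "with a two-sided alpha level of 0.05 and statistical power (1–β) of 90%, the estimated sample size is 200 patients".
- **The Abstract** hypothesises that telerehabilitation is non-inferior to standard rehabilitation. **Section 10 (Expected Results)** instead expects a significant improvement relative to the in-person group. Neither gives a non-inferiority margin or a one-sided alpha.

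**The concern.** A confidence interval and a test of the same parameter agree when the confidence level is one minus the two-sided alpha. Two-sided 0.05 goes with 95%; a 90% interval goes with two-sided 0.10, or 0.05 in each tail. The plan therefore attaches two error rates to one comparison and does not say why.

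Readers routinely check whether an interval for an odds ratio covers 1. Here some results would show an interval clear of 1 beside a p-value that the plan calls non-significant. Allocation is by patient preference, and the aim is worded as non-inferiority in one place and as improvement over the in-person arm in another. An unexplained interval level then leaves room to choose the more favourable reading after the results are known.

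**Working it through.** **Inputs from the article.** Confidence level 90% (Section 9.1); two-sided significance level 0.05 (Sections 9.2 and 9.3); power 90% and 200 patients before dropout (Section 9.3).

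**The plan's own figure.** The enrolment target follows as 200 × 1.10 = 220. The 200 can be neither reproduced nor refuted, because the article gives no standard deviation and no responder rates. Nothing below depends on it.

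**Step 1: critical values.** A Wald interval for a log odds ratio is estimate ± z × SE.
- 90% interval: z(0.95) = 1.645.
- 95% interval: z(0.975) = 1.960.

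**Step 2: relative width.** The SE cancels: 1.645 / 1.960 = 0.84. The 90% interval is 16% narrower on the log scale.

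**Step 3: where interval and test disagree.** The 90% interval excludes 1 when |z| > 1.645 (p < 0.10). The stated test is significant when |z| > 1.960 (p < 0.05). They part company for 0.05 ≤ p < 0.10.

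**Step 4: how often.**
- No difference: 0.10 − 0.05 = 0.05, or 5% of trials.
- An effect for which the test has 90% power: the expected z is 1.960 + 1.282 = 3.242. The chance of landing in the gap is Φ(1.960 − 3.242) − Φ(1.645 − 3.242) = 0.100 − 0.055 ≈ 0.045, or about 4.5%.

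**Step 5: illustration.** The counts are assumed, since the article gives no responder rates: 100 per arm, 50 responders against 63, unadjusted.
- Odds ratio = (63/37) / (50/50) = 1.70; log odds ratio = 0.532.
- SE = √(1/50 + 1/50 + 1/63 + 1/37) = 0.288.
- z = 0.532 / 0.288 = 1.85; two-sided p = 0.064.

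| Interval | Limits | Covers 1? |
|---|---|---|
| 90% | 1.06 to 2.73 | no |
| 95% | 0.97 to 2.99 | yes |

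Other assumed counts behave alike: 50 against 62 gives p = 0.088 and a 90% interval of 1.02 to 2.62 (95%: 0.93 to 2.86); 40 against 53 gives p = 0.066 and 1.06 to 2.71 (95%: 0.97 to 2.96). In each case the 95% interval agrees with the test.

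**The case against.** **Non-inferiority.** The strongest defence is that a two-sided 90% interval is the usual companion of a one-sided 5% non-inferiority test, and the Abstract does hypothesise non-inferiority. That is the only plausible rationale in the document, and with a declared margin and a one-sided alpha of 0.05 it would be coherent. But the article states neither. The alpha it does state is two-sided 0.05, which implies 2.5% per tail, whereas a 90% interval leaves 5%. Under non-inferiority the bound would also be compared with a margin rather than with 1. The defence explains how the 90% may have arisen; it does not reconcile it with the rest of the plan.

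**The p-value decides.** Section 9.1 only reports the interval and bases no decision on whether it covers 1. This stands. A reader might infer that the plan's type I error is 10%; the document does not support that, because Section 9.2 defines significance by the p-value alone.

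**Placement.** The significance sentence sits under the secondary-endpoint heading. Its scope, however, is all final analyses, and Section 9.3 separately applies two-sided 0.05 to the primary endpoint.

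**A slip from the power figure.** A reader might also guess that 90% was carried over from the 90% power. Nothing in the text shows this, and the point does not need it.

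**Conclusion.** The concern holds as a mismatch in reporting level. The article fixes a 90% interval for its only between-arm primary estimate, fixes two-sided 0.05 for testing and sizing, and gives no reason for the difference.

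The effect is limited. The significance test, the model and the sample size are untouched. Discordant results have a probability of 5% under no difference and about 4.5% at an effect detected with 90% power. The error rate doubles from 5% to 10% only if the interval replaces the p-value as the criterion for a difference. For a non-inferiority claim, doubling (2.5% to 5% per tail) follows only if one-sided 0.025 is taken from the stated two-sided 0.05, since the article gives no non-inferiority alpha.

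These figures assume a Wald interval and Wald test under the normal approximation. The illustrative counts are assumptions and show only the pattern. The correction is worth making because this interval will carry the trial's comparative conclusion.

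**What to change.** In Section 9.1, replace the 90% interval for the primary odds ratio with a 95% interval, matching the two-sided 0.05 in Sections 9.2 and 9.3.

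If non-inferiority is the intended aim, state that in the statistical section, declare the margin and the one-sided alpha before the analysis, and derive the interval level from that alpha (level = 1 − 2 × one-sided alpha). Bring Sections 9.2, 9.3 and 10 into line with it.

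The first option changes one number. It needs no new data and no new model, because both intervals come from the same estimate and standard error. Its only downside is a wider reported interval, by a factor of 1.960 / 1.645 = 1.19 on the log scale. The second option requires a margin that the article does not contain and a check of the sample size against it. The Data Availability statement says data collection is ongoing, so either change can be documented before the final analysis.

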### 9.2. Secondary Endpoint Analysis

Continuous variables will be presented as mean ± standard deviation for normally distributed variables, and as median and interquartile range for those with non-normal distribution. Categorical data will be expressed as absolute numbers and percentages. The Shapiro–Wilk test will be used to assess normality.

For repeated measurements (e.g., QoL scores, biochemical markers, functional parameters), comparisons across timepoints (T0, T1, T2, T3, T4) will be conducted using one-way repeated measures ANOVA for normally distributed data, or Friedman test for non-parametric data.For post hoc comparisons, Bonferroni correction will be applied to control for type I error.Categorical variables (e.g., proportion of patients with adverse events) will be compared using the Pearson chi-square test or Fisher’s exact test where appropriate.

A two-sided *p*-value < 0.05 will be considered statistically significant for all final analyses.

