Cool-down (10 min)	- 5 min stretching scapular/pelvic muscles - 5 min breathing with Khymeia spirometer	- 5 min stretching scapular/pelvic muscles - 5 min breathing with volumetric incentive spirometer

**Table 3 healthcare-13-02074-t003:** Outcome Measures by Timepoint.

Outcome Type	Outcome Measure	Unit of Measure	Domain	Clinical Relevance/Rationale	T0 (Baseline)	T1 (4 wks)	T2 (8 wks)	T3 (12 wks)	T4 (24 wks)
Primary	≥10% improvement in VO_2_max (CPET)	mL/kg/min	Functional Capacity	Gold standard for evaluating aerobic capacity and predicting prognosis in CHF	✔		✔	✔	✔
Secondary	Change in body weight	Kg	Anthropometric	Important for monitoring nutritional status; weight fluctuations are clinically relevant predictors of CHF decompensation.	✔	✔	✔	✔	✔
Secondary	Change in BMI	kg/m^2^	Anthropometric	Static measure to stratify overweight, obesity, which may influence exercise response and prognosis in CHF	✔	✔	✔	✔	✔
Secondary	Change in KCCQ-12 Score	Points (0–100)	QoL	CHF-specific QoL instrument sensitive to clinical changes	✔	✔	✔	✔	✔
Secondary	Change in SF-36 Score	Points (0–100)	QoL	Generic QoL questionnaire for broader health-related QoL	✔	✔	✔	✔	✔
Secondary	Change in 6MWT	Meters	Functional	Test of submaximal exercise capacity; reflects improvements in daily functional status	✔	✔	✔	✔	✔
Secondary	Change in SPPB Score	Points (0–12)	Functional	Assesses lower extremity strength, balance, and mobility—predictive of disability and frailty	✔	✔	✔	✔	✔
Secondary	Change in MMSE	points (0–30)	Cognitive	Screens for cognitive impairment, which can affect adherence and prognosis in CHF patients.	✔	✔	✔	✔	✔
Secondary	Change in BNP	pg/mL	Biochemical	Established biomarkers of myocardial stress; reflect CHF severity and response to therapy.	✔		✔	✔	✔
Secondary	Change in NT-proBNP	pg/mL	Biochemical	Established biomarkers of myocardial stress; reflect CHF severity and response to therapy.	✔		✔	✔	✔
Secondary	Change in Serum Creatinine	mg/dL	Biochemical	Monitor renal function, critical in CHF management due to cardiorenal interactions and therapy impact	✔		✔	✔	✔
Secondary	Change in eGFR	mL/min/1.73 m^2^	Biochemical	Monitor renal function, critical in CHF management due to cardiorenal interactions and therapy impact	✔		✔	✔	✔
Secondary	Change in Serum Sodium	mmol/L	Biochemical	Important for assessing treatment safety (e.g., diuretics, ACE inhibitors) and arrhythmic risk	✔		✔	✔	✔

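### A normality pre-test picks the secondary analysis method, and neither method it can pick suits BNP and NT-proBNP; a pre-specified log-scale analysis would gain about 11 to 13 points of power

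*Protocol article*

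**What the plan says.** Section 9.2 (Secondary Endpoint Analysis) gives one normality criterion: "The Shapiro–Wilk test will be used to assess normality". The next paragraph covers repeated measurements of quality-of-life scores, biochemical markers and functional parameters, and assigns them to "one-way repeated measures ANOVA for normally distributed data, or Friedman test for non-parametric data". Post hoc comparisons are Bonferroni-corrected, without naming the pairwise test. Non-normal variables are summarised "as median and interquartile range for those with non-normal distribution".

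Section 9.1 has the same kind of switch for VO2max: a paired t-test, with this fallback: "For non-normally distributed data, the Wilcoxon Signed-Rank test will be applied". It does not name Shapiro–Wilk.

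Table 3 schedules BNP and NT-proBNP at four visits (T0, T2, T3, T4) and the questionnaires, 6MWT, SPPB and MMSE at five. SPPB runs from 0 to 12, MMSE from 0 to 30, and KCCQ-12 and SF-36 from 0 to 100. Section 9.3 plans 200 evaluable patients.

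**The concern.** A significance test of normality answers a different question from the one that matters, namely whether a method is adequate for the outcome. Its verdict also depends on sample size. With 100 to 200 observations it rejects nearly every skewed biomarker and short integer score, so for those outcomes the fallback is in effect the planned analysis. For a score that is only mildly non-normal, chance and the number of patients tested decide whether a mean change or a rank shift is reported.

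The natriuretic peptides are where this costs most. The Background makes biological response to training a study aim, and Expected Results anticipates favourable changes in BNP and NT-proBNP. Under the stated rule they are analysed either as raw values, where a few large readings dominate, or by within-patient ranks, which discard the size of the change. The usual scale for such data, the logarithm, is not one of the two choices.

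**Working it through.** **Inputs from the document.** 200 evaluable patients (Section 9.3); k = 4 visits for BNP and NT-proBNP, k = 5 for SPPB, MMSE and KCCQ-12 (Table 3); two-sided 0.05 (Section 9.2).

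**Assumptions, since the document gives no dispersion.** Shapiro–Wilk at 0.05; about 100 patients per arm if arms are tested separately and 200 if pooled; log-normal peptides; clipped (for SPPB and MMSE also rounded) normal distributions for the scores. The document states no efficiency or power figure for these tests, so there is none to reproduce.

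**Step 1: what the pre-test does at this size.** Simulated rejection rates:

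| Assumed distribution | n = 100 | n = 200 |
|---|---|---|
| Log-normal, log SD 0.3 | 86% | 99.5% |
| Log-normal, log SD 0.5 or more | 99.9–100% | 100% |
| SPPB-like, means 8 to 10 | 99.5–100% | 100% |
| MMSE-like, means 26 to 28 | 100% | 100% |
| KCCQ-like, mean 50, SD 20 | 3% | 4% |
| KCCQ-like, mean 60, SD 22 | 14% | 55% |
| KCCQ-like, mean 70, SD 22 | 87% | 100% |

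Testing changes instead of raw values does not alter the result for the peptides: with between-patient log SD 1.0 and within-patient log SD 0.35 or 0.45, Shapiro–Wilk rejected about 100% of samples of raw-scale differences as well.

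**Step 2: asymptotic efficiency.** Relative to repeated-measures ANOVA on a scale where within-patient errors are normal, Friedman has efficiency 3k / (π(k + 1)).

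- k = 4: 12 / (5π) = 0.764, a loss of about 24%. Matching 100 patients takes 100 / 0.764 ≈ 131.
- k = 5: 15 / (6π) = 0.796, a loss of about 20%.

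For the peptides the reference is ANOVA on log values.

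**Step 3: simulated power for NT-proBNP.** Four visits, 200 patients, 10% fall at every visit after baseline, between-patient log SD 1.0:

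| Within-patient log SD | Raw-scale ANOVA | Friedman | Log-scale ANOVA |
|---|---|---|---|
| 0.35 | about 45% | about 77% | about 88% |
| 0.45 | about 30% | about 55% | about 68% |

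Repeat runs moved these by up to about 3 points. With 100 patients, within-patient log SD 0.3 and a shift of −0.13 on the log scale (a fall of 1 − exp(−0.13) ≈ 12%), the three powers were 52%, 77% and 89%; Friedman needed about 126 to 131 patients to reach the log-scale figure.

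**Step 4: simulated power for the scores.** Five visits, 100 patients, Friedman against ANOVA on the score itself: SPPB-like 88% against 92%, MMSE-like 89% against 93%, KCCQ-like (mean 70) 89% against 95%.

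**The case against.** **The rule picks the better of its two methods for the peptides.** A reader might infer from the efficiency loss that Friedman is the worst choice for BNP and NT-proBNP. The document does not support that. The plan's other method is ANOVA with no stated transformation, and against that Friedman gains clearly (about 77% against 45%). The loss exists only against a log-scale analysis. This part of the objection stands, so the complaint must be that neither planned option suits.

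**Not every bounded score is sent to Friedman, and not every score loses a fifth.** KCCQ-12 and SF-36 are bounded too, and a score centred mid-scale usually passes the check. For SPPB and MMSE the simulated loss is about 3 to 5 points of power. Both corrections stand.

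**The plan does report more than a p-value.** Medians with interquartile ranges are given and post hoc comparisons are planned, so it would be wrong to say that nothing descriptive accompanies the test. What is missing under Friedman is an estimate of change with an interval.

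**Testing of raw values is not stated.** Shapiro–Wilk appears in the paragraph on descriptive statistics, and the article does not say whether it is applied to raw values, changes or residuals. Its role as selector is inferred, though strongly: it is the only criterion given and the next sentences depend on it. It would be unfair to charge the plan with testing the wrong quantity. As Step 1 shows, testing raw-scale changes leads to the same place for the peptides.

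**Transformations belong in the SAP.** The absence of a log-scale statement from an article is indeed no fault. The normality-driven choice, however, is written down as the rule, and it can be judged as written.

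**Conclusion.** The point holds, at the level of a cheap improvement. The stated rule makes a significance test of normality the selector of method and of the quantity reported. At 100 to 200 patients this is close to certain to send BNP and NT-proBNP to Friedman, likewise SPPB and MMSE under the assumed ceilings, and it leaves KCCQ-12 partly to chance.

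The material cost is confined to the natriuretic peptides: about 76% of the efficiency of a log-scale analysis, or roughly 11 to 13 points of power at 200 patients for a 10% fall, and no estimate of change with an interval. For SPPB and MMSE the loss is small.

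The powers rest on assumed log-normality, dispersions and effect size. They concern change over time in one pooled group, which is what a one-way repeated-measures test addresses; they say nothing about the comparison between arms. With about 100 patients per arm the absolute powers for a 10% fall would be lower for all three methods, in the same order. For VO2max in Section 9.1 the same habit is visible, but no loss was calculated and none is claimed.

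**What to change.** Remove the normality test as method selector. State in advance that BNP and NT-proBNP are analysed on the log scale and reported as ratios of geometric means with confidence intervals, and that the other outcomes are analysed on their own scale, all in one pre-specified form of longitudinal model. Check residuals by plot. Keep Friedman and Wilcoxon as sensitivity analyses.

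The cost is a few sentences in the analysis plan. No visit, measurement or sample size changes. The one drawback is that ratios of geometric means need a line of explanation for readers.

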## Abstract

**Background:** Despite strong guideline recommendations, participation in cardiac rehabilitation (CR) among patients with chronic heart failure (CHF) remains low due to logistical, geographical, and psychosocial barriers. Telerehabilitation may help overcome these limitations by offering remote, structured exercise programs supported by digital technologies. **Objective:** The TELEREHAB-HF study aims to evaluate the efficacy of an 8-week, home-based cardiac telerehabilitation program compared to standard in-person rehabilitation in patients with CHF. **Methods:** This is a prospective, controlled cohort study involving 220 adult patients with CHF (NYHA class I–III) clinically stable and on optimized therapy. Participants are assigned to either a telerehabilitation group (remote CR via a digital platform with wearable sensors and real-time physiotherapist supervision) or a standard in-person rehabilitation group. The primary outcome is the change in peak oxygen uptake (VO_2_max) at 8 weeks. Secondary outcomes include quality of life, functional performance, biochemical and echocardiographic parameters, and cognitive function, assessed at baseline and at 4, 8, 16, and 24 weeks. **Expected Results**: We hypothesize that telerehabilitation will be non-inferior to standard CR in improving functional capacity and secondary outcomes, with additional benefits in accessibility and adherence. Data from remote monitoring may also support a translational “rehabilomics” approach to exploring exercise-induced biomarker changes. **Conclusions:** This study seeks to assess the clinical effectiveness, safety, and feasibility of a home-based telerehabilitation model for CHF, with the goal of informing future strategies for broader implementation and personalized rehabilitation. Trial Registration: ClinicalTrials.gov Identifier: NCT07023536

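### The only test named for repeated continuous secondary outcomes has no arm term, so it cannot address the hypothesis that telerehabilitation is non-inferior on them

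*Protocol article*

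**What the plan says.** The hypothesis, in the abstract, is that "telerehabilitation will be non-inferior to standard CR in improving functional capacity and secondary outcomes". It compares the two arms and includes the secondary outcomes.

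Section 9.2 opens its inferential part with "For repeated measurements (e.g., QoL scores, biochemical markers, functional parameters" and then says that "comparisons across timepoints (T0, T1, T2, T3, T4) will be conducted using one-way repeated measures ANOVA for normally distributed data, or Friedman test" will be used. It continues: "For post hoc comparisons, Bonferroni correction will be applied to control for type I error". It names no contrasts for that step and does not say whether the tests are run on all patients or within each arm.

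The only other outcome test in 9.2 is this: "Categorical variables (e.g., proportion of patients with adverse events) will be compared using the Pearson chi-square test or Fisher’s exact test where appropriate".

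The arm enters a named model once, in section 9.1, where the logistic regression for the primary responder endpoint is fitted "with “Rehabilitation Type (Telerehabilitation vs. Standard)” as the main predictor". Section 2 promises statistical adjustment, with propensity scores as the example, and section 12 mentions matching. Neither is tied to a model for a secondary outcome. Section 9.3 adds that the sample size "allows for robust evaluation of secondary outcomes including QoL, echocardiographic and biochemical parameters".

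**The concern.** A one-way repeated-measures ANOVA asks whether the mean changes between visits, and the Friedman test asks the same of within-patient ranks. Neither contains arm, arm-by-visit or a covariate, so neither estimates a difference between telerehabilitation and in-person rehabilitation.

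Sections 2 and 3 give both arms an 8-week supervised exercise programme of the same structure and intensity. Improvement over time is therefore expected in both. On instruments given up to five times, such as the 6MWT and MMSE, part of it may be practice.

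Two misreadings are at stake:

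- A pooled time effect can be significant while the remote arm does clearly worse than the in-person arm.
- Separate tests by arm can suggest a difference where none exists.

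Allocation follows patient preference and logistics, so an unadjusted contrast would also be open to confounding. The stated test offers no arm effect to adjust.

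**Working it through.** **1. Scope.** Section 9.2 names QoL, biochemical and functional measures, as examples. Table 3 also schedules MMSE, echocardiographic and anthropometric measures repeatedly, and no other inferential method for continuous secondary outcomes is given. Including them is a fair inference, not stated text.

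**2. Plan's own figure.** None is stated for any secondary outcome. The 200 patients in section 9.3 belong to the primary endpoint and are used below only as a total.

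**3. What the time test can see.** Simulation with assumed inputs: 1,000 trials, 100 per arm, five visits, SD 1, between-visit correlation 0.6, half the gain at the second visit and the full gain from the third. The entries are the share of trials with p < 0.05.

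| True gain, in-person / remote (SD) | Time test, pooled | Time test, remote arm only | Arm-by-time test |
|---|---|---|---|
| 0.5 / 0.5 | 100% | 100% | 4.6% |
| 0.8 / 0.2 | 100% | 58% | 100% |
| 1.0 / 0 | 100% | 4.4% | 100% |

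The pooled time test gives the same answer whether the arms gain equally or the remote arm gains nothing.

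**4. Separate tests by arm.** With equal true effects, power p in each arm and independent arms, the chance that exactly one arm is significant is 2p(1 − p):

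- p = 0.8: 2 × 0.8 × 0.2 = 0.32
- p = 0.5: 2 × 0.5 × 0.5 = 0.50

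**5. One KCCQ-12 scenario.** Assumed: 100 per arm, SD of change 15, true gain +3 remote and +10 in-person, two-sided 5%, power Φ(δ/SE − 1.96). These are z-tests of a single change score, simpler than the five-visit ANOVA.

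- Remote arm only: SE = 15/√100 = 1.5; 3/1.5 = 2.00; power 52%.
- Pooled: the mean gain is 6.5 and each arm lies 3.5 from it; SE = √(15² + 3.5²)/√200 = 1.09; 6.5/1.09 = 5.97; power above 99%.
- Between arms: SE = 15 × √(2/100) = 2.12; 7/2.12 = 3.30; power 91%.

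**6. Range for the between-arm test.**

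| Gap (points) | SD | Arms | SE | Gap/SE | Power |
|---|---|---|---|---|---|
| 7 | 15 | 100/100 | 2.12 | 3.30 | 91% |
| 5 | 15 | 100/100 | 2.12 | 2.36 | 65% |
| 3 | 15 | 100/100 | 2.12 | 1.41 | 29% |
| 7 | 20 | 100/100 | 2.83 | 2.47 | 70% |
| 7 | 15 | 50/150 | 2.45 | 2.86 | 82% |

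The last row uses SE = 15 × √(1/50 + 1/150). It matters because allocation by preference need not give equal arms. Any precision lost to propensity adjustment comes on top.

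**7. What non-inferiority would also need.** No margin is given for any outcome. At one-sided 0.025 and a true difference of zero, the margin in SD units that 100 per arm supports is (1.96 + z) × √(2/100):

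- 90% power: (1.96 + 1.28) × 0.1414 = 0.46 SD
- 80% power: (1.96 + 0.84) × 0.1414 = 0.40 SD

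For 90% power, margins of 0.2, 0.3, 0.4 and 0.5 SD need 1052, 468, 264 and 170 patients in total. The 10% in section 9.3 is a difference to detect in VO2max, and it cannot serve as a margin for KCCQ-12 or BNP.

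**The case against.** The strongest defence has four parts.

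- **Between-arm comparison is clearly intended.** The adjustment promised in section 2 is not limited to the primary outcome, and section 12 adds matching. This stands as far as it goes: a reader might infer that the plan disregards the arms, and the documents do not support that. But a promise of adjustment supplies no test, and the method that 9.2 names has no arm effect to adjust.
- **The secondary non-inferiority claim rests on one sentence of the abstract.** Section 10 expects only favourable trends, and section 8 speaks of longitudinal evaluation of both programmes. A time test is of some use for those aims. The abstract's hypothesis still stands in the plan, and 9.2 applies a significance threshold to all final analyses. The sentence from section 9.3 adds little, because it states no between-arm aim.
- **Detail may be left to an analysis plan that is not shown.** That would answer silence. Here the article names a specific method, and the method does not fit the question.
- **The figures depend on chosen inputs.** This is right. The SD, gaps, correlation and equal arms are assumptions, so a range is shown. The 32% and 50% apply only if the tests are run by arm, which 9.2 does not say. That the post hoc comparisons are between visits is likewise only the probable reading.

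A reader might also infer that no secondary result bears on the comparison. That goes too far: adverse events are a secondary outcome, and the chi-square or Fisher test can compare them between arms. Even so, a non-significant difference there would not show non-inferiority.

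**Conclusion.** The point holds for the repeated continuous secondary outcomes. The method stated for them cannot address the stated hypothesis, whether it is run pooled or by arm. This follows from the absence of an arm term and depends on none of the assumed numbers.

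The numbers show only what is at stake. A pooled time test can be significant in practically every trial while the remote arm gains nothing. Separate tests by arm would disagree in 32% of trials with equal effects at 80% power each. A direct comparison with 100 per arm has 29% to 91% power for KCCQ-12 gaps of 3 to 7 points at an assumed SD of 15, about 70% for 7 points at SD 20, and less if the arms are unequal.

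Two stronger conclusions are not supported. The primary logistic analysis has an adjusted arm term and is not affected by this point. And adding an arm term would not by itself test non-inferiority, because no margin exists in the document.

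**What to change.** 1. In section 9.2, make the main analysis of each continuous secondary outcome a between-arm comparison, adjusted for the baseline value and for the same propensity score or covariates as the primary analysis. A longitudinal mixed model with arm, visit and arm-by-visit serves all visits scheduled for that outcome; a baseline-adjusted ANCOVA at week 8 is a simpler alternative for that visit.
2. Report the adjusted difference with its confidence interval at week 8 and at the follow-up visits T3 and T4.
3. Keep within-arm change over time as description, without conclusions drawn from one arm being significant and the other not.
4. Settle the hypothesis in one of two ways. Either pre-state a non-inferiority margin, with its justification, for each secondary outcome that carries the claim, and check that about 100 per arm can support it. Or restrict non-inferiority to the primary outcome and present secondary differences as estimates with intervals.

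The cost is protocol and analysis-plan wording plus standard code. Restricting the hypothesis needs no new data and no new patients. Keeping secondary non-inferiority also needs margins to be agreed, and margins much below about 0.4 SD would be out of reach at this sample size.
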